### **8.3 Clinical Laboratory AEs, and SAEs**

Abnormal laboratory findings (e.g. clinical chemistry, haematology, urinalysis) or other abnormal assessments (e.g. ECG, vital signs) that are judged by the Investigator as clinically significant will be recorded as AEs or SAEs if they meet the definition of an AE, as defined in Section 8.1, or SAE as defined in Section 8.2.

Clinically significant abnormal laboratory findings or other abnormal assessments that are detected during the study or are present at Baseline and significantly worsen following the start of the study will be reported as AEs or SAEs. However, clinically significant abnormal laboratory findings or other abnormal assessments that are associated with a disease reported in the medical history, unless judged by the Investigator as more severe than expected for the Participant's condition, or that are present or detected at the start of the study and do not worsen, will not be reported as AEs or SAEs.

The Investigator will exercise their medical and scientific judgement in deciding whether an abnormal laboratory finding or other abnormal assessment is clinically significant.

### **8.4 Time Period, Frequency, and Method of Detecting AEs and SAEs**

All AEs will be recorded between the time of consent and the follow-up visit. Each Participant will be monitored regularly by the Investigator and study personnel for AEs occurring throughout the study. During the treatment period, the Investigator or designee will enquire about AEs by asking the following non-leading questions:

At each visit Participants will be asked:

“How are you feeling?”

At subsequent scheduled intervals Participants will be asked:

“Since you were last asked, have you felt unwell or different from usual?”

### **8.5 Recording of AEs and SAEs**

When an AE/SAE occurs, it is the responsibility of the Investigator to review all documentation (e.g. hospital progress notes, laboratory, and diagnostic reports) related to the event. The Investigator will then record all relevant information regarding an AE/SAE in to the eCRF. It is

not acceptable for the Investigator to send photocopies of the Participant's medical records to the Sponsor in lieu of completion of the appropriate AE/SAE CRF pages. However, there may be instances when copies of medical records for certain cases are requested by the Sponsor. In this instance, all Participant identifiers will be removed and the study number, Participant's initials, and randomisation number will be written on the copies of the medical records prior to submission to the Sponsor.

For each AE, start and stop dates, action taken, outcome, intensity (see Section 8.8.1), and relationship to study product (causality) (see Section 8.8.2) must be documented. If an AE changes in frequency or intensity during a study, a new entry of the event must be made in the eCRF.

The Investigator will attempt to establish a diagnosis of the event based on signs, symptoms, and/or other clinical information. In the absence of a diagnosis, the individual signs/symptoms should be documented.

All details of any treatments initiated due to the AE should be recorded in the Participant's notes and the eCRF.

## **8.6 Prompt Reporting of SAEs**

Once an Investigator becomes aware that an SAE has occurred in a study Participant, they will immediately notify the Sponsor of the event. The SAE form must be completed as thoroughly as possible with all available details of the event, signed by the Investigator (or appropriately qualified designee), and faxed to the Sponsor within 24 hours of first becoming aware of the event.

If the Investigator does not have all information regarding an SAE, they will not wait to receive additional information before notifying the Sponsor of the event and completing the form. The form will be updated when additional information is received.

The Investigator will always provide an assessment of causality at the time of the initial report as described in Section 8.8.2, "Assessment of Causality". If data obtained after reporting indicates that the assessment of causality is incorrect, then the SAE form may be appropriately amended, signed and dated, and resubmitted to the Sponsor.

In accordance with local requirements, the Investigator must also notify the Human Research Ethics Committee (HREC) who approved the study of any SAEs (according the guidelines of the HREC).

The Investigator, and others responsible for Participant care, should institute any supplementary investigations of serious adverse events based on their clinical judgement of the likely causative factors. This may include seeking further opinion from a specialist in the field of the AE. The Sponsor may also request extra tests. If a Participant dies, any post-mortem findings, including histopathology will be provided to the Sponsor when available. No medical help, diagnosis, or advice should be withheld from the Participant due to an inability to contact the Sponsor.

## **8.7 Expeditable Events**

Expeditable events are those AEs that are **CAUSALLY** related to the study product, **AND** that are both **SERIOUS** (see Section 8.2) and **UNEXPECTED** (see Section 8.8.3). Such events are to be expedited to regulatory authorities and will be reported within the stipulated timelines by the Sponsor or a suitably qualified designee.

## **8.8 Evaluating AEs and SAEs**

### **8.8.1 Assessment of Intensity**

The Investigator will make an assessment of intensity for each AE and SAE reported during the study. The assessment will be based on the Investigator's clinical judgement. The intensity of each AE and SAE recorded in the eCRF should be assigned to one of the following categories:

**Mild:** An event that is easily tolerated by the Participant, causing minimal discomfort and not interfering with everyday activities.

**Moderate:** An event that is sufficiently discomforting to interfere with normal everyday activities.

**Severe:** An event which is incapacitating and prevents normal everyday activities.

An AE that is assessed as severe should not be confused with an SAE. Severity is a category utilised for rating the intensity of an event; and both AEs and SAEs can be assessed as severe. An event is defined as "serious" when it meets one of the pre- defined outcomes as described in Section 8.2 "Definition of an SAE".

### **8.8.2 Assessment of Causality**

The Investigator is obligated to assess the relationship between IP and the occurrence of each AE/SAE. The Investigator will use clinical judgment to determine the relationship. Alternative

causes, such as natural history of the underlying diseases, concomitant therapy, other risk factors, and the temporal relationship of the event to the IP will be considered and investigated. The Investigator will also consult the IB and/or product information in the determination of their assessment.

The causal relationship to the study product assessed by the Investigator (or medically qualified delegate) should be assessed using the following classifications:

- Not Related** In the Investigator's opinion, there is not a causal relationship between the study product and the AE.
- Unlikely** The temporal association between the AE and study product is such that the study product is not likely to have any reasonable association with the AE.
- Possible** The AE could have been caused by the study Participant's clinical state or the study product.
- Probable** The AE follows a reasonable temporal sequence from the time of study product administration, abates upon discontinuation of the study product and cannot be reasonably explained by the known characteristics of the study Participant's clinical state.
- Definitely** The AE follows a reasonable temporal sequence from the time of study product administration or reappears when study product is reintroduced.

There may be situations when an SAE has occurred and the Investigator has minimal information to include in the initial report to the Sponsor. However, it is very important that the Investigator always makes an assessment of causality for every event prior to transmission of the SAE form to the Sponsor. The Investigator may change their opinion of causality in light of follow-up information, amending the SAE form accordingly. The causality assessment is one of the criteria used when determining regulatory reporting requirements.

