#### Secondary Objectives

1. The effect of each product and the combination of products absolute on weight loss (kg) and percentage of weight loss, relative to baseline body weight.
2. To examine the changes in full lipid profile (including total cholesterol, high-density lipoprotein (HDL), low-density lipoprotein (LDL)), apolipoprotein B, plasma glucose, and glycated haemoglobin (HbA1c) between groups.
3. To compare the percentage of Participants in each category of glucose tolerance (normal, impaired fasting glucose, and type 2 diabetes) between groups at study completion.
4. To examine changes in body composition by waist circumference, fat mass, fat free mass, and blood pressure between groups.
5. To examine the changes in other biochemical parameters (liver enzymes and inflammatory markers) between groups.
6. To measure the side effect profile of each product using adverse event (AE) reporting.
7. To investigate the change in vitality between groups using the vitality scale of the short form (SF) SF-36 Health Survey.
8. To investigate the relationship between goals, outcome-expectancies, self-efficacy, commitment and weight change across all groups
9. To investigate the relationship between unmet goals, effort, dissatisfaction and weight change across all groups.
10. To investigate the effect of the intervention type on changes in personality (Five Factor Model, self-efficacy) and preferences (risk and time).
11. To investigate whether efficacy of the intervention type depends on the change in personality/preferences.
12. To determine the cost-effectiveness of each intervention relative to the lifestyle programme alone by measuring the cost per quality adjusted life year (QALY).

13. To determine whether weight loss results in better financial outcomes for Participants
14. To measure the change in gut hormones and adipokines between groups.
15. To investigate the long-term outcome of the gut microbiota profile between all groups.
16. To compare the metabolic activity of gut microbiota between groups (short chain fatty acids (SCFA) production in plasma and faeces).
17. To investigate the dynamics of the microbiota community as a result of dietary supplementation and elimination of FBCx and Ginst15 across all groups.
18. To determine the difference in handgrip strength throughout the study.

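### In the causality scale of Protocol 8.8.2, the top grade (Definitely) can be met by timing alone, a weaker test than the grade below it (Probable), so the two grades are not ordered

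*Protocol*

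**What the plan says.** Protocol 8.8.2 gives investigators five grades: Not Related, Unlikely, Possible, Probable and Definitely. The upper three, from the top down, are defined as follows.

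- Definitely, the highest, reads: "The AE follows a reasonable temporal sequence from the time of study product administration or reappears when study product is reintroduced".
- Probable asks for three things together: plausible timing, abatement once product is stopped, and an event that "cannot be reasonably explained by the known characteristics of the study Participant's clinical state".
- Possible is the loosest of the three and asks for no more than this: "The AE could have been caused by the study Participant's clinical state or the study product".

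The section opens with a general instruction: "The Investigator will use clinical judgment to determine the relationship". It adds that other causes, such as underlying disease, concomitant therapy and other risk factors, are to be considered and investigated.

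The grade is used elsewhere. Section 8.5 requires causality to be documented for each adverse event. Section 8.6 requires a causality assessment with the initial report of a serious event, on a form due within 24 hours. Section 8.7 covers events that are causally related, serious and unexpected: "Such events are to be expedited to regulatory authorities". Secondary objective 6 in section 3 is "To measure the side effect profile of each product using adverse event (AE) reporting".

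**The concern.** A causality scale is read as a ladder, in which a higher grade should need at least as much evidence as the one beneath it. Here the step from Probable to Definitely drops two requirements, abatement and the absence of another explanation, and offers recurrence on reintroduction only as an alternative to timing. No other part of the protocol corrects the 'or' or says which grade applies when an event meets two definitions.

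What is at stake is the grade recorded for individual events. An investigator who follows the definition literally could place an event with good timing, no dechallenge information and a plausible competing cause in the top grade. A colleague who follows the general instruction on alternative causes could call the same event Possible. Both could defend their choice from the text. The grade is assigned when the data are captured, so a later analysis plan could not recover which criteria had been applied.

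**Working it through.** The protocol gives no figure to reproduce here, and no power or alpha input is involved. The check is logical.

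**Inputs, all from Protocol 8.8.2.** Four yes/no criteria appear in the two upper definitions:

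- T: reasonable timing relative to administration
- D: abates on discontinuation
- N: not reasonably explained by the participant's clinical state
- R: reappears on reintroduction

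Four binary criteria give 2 × 2 × 2 × 2 = 16 patterns.

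**Rules as written.**

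- Probable = T and D and N, with R free: 2 patterns.
- Definitely = T or R. T present gives 8 patterns; T absent with R present gives 4; the total is 8 + 4 = 12.

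**Comparison.**

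- Both Probable patterns contain T, so both also meet Definitely. Probable is a strict subset of the grade above it.
- 12 − 2 = 10 patterns meet Definitely but fail Probable.
- One of these ten is timing alone (T yes; D, N and R no). N is absent, so the clinical state is a reasonable explanation, and the event also fits Possible. It therefore meets the third and the fifth grade but not the fourth.

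**If product is never reintroduced** (R = no), 8 patterns remain. Definitely reduces to T and is met by 4; Probable is met by 1. The disorder does not depend on rechallenge occurring.

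**Candidate repairs.**

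| Definition of Definitely | Patterns met | Of these, also meeting Probable |
|---|---|---|
| T or R (as written) | 12 | 2 |
| T and R ('or' changed to 'and') | 4 | 1 |
| T and D and N and R | 1 | 1 |

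Changing the conjunction alone is not enough, because 4 − 1 = 3 of the qualifying patterns would still fail Probable. Only the last row places Definitely inside Probable.

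These are counts of logical combinations, each counted once. They show how the definitions relate and do not estimate what share of events would be affected.

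**The case against.** The strongest reply is that section 8.8.2 does not leave the investigator alone with one line. Clinical judgement and the investigation of other causes govern every grade, and a sensible investigator will not call an event definite on timing alone. This stands as a limit on the practical effect. It does not repair the definition: the general instruction says to weigh other causes, the top grade omits them, and nothing says which prevails.

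Three stronger readings are tempting, and the protocol does not support them.

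- *The side-effect profile is misclassified, and product effects cannot be separated from background.* Objective 6 refers to adverse event reporting, and the protocol does not say events will be tabulated or filtered by causality grade. In a double-blind, placebo-controlled factorial trial, all adverse events can be compared between arms without using the grade. Blinding also leaves no evident reason for over-grading to differ by arm.
- *Nearly every on-treatment event would qualify, because product is taken three times a day for 168 days (section 7.4).* Being on treatment is not the same as reasonable timing. Unlikely is itself defined by a poor temporal association, so the scale expects some on-treatment events to fail the timing test. No figure supports 'nearly every'.
- *Expedited reporting is shown to be wrong.* Section 8.7 also requires seriousness and unexpectedness, and it sets no threshold among Possible, Probable and Definitely. Movement between those grades is not shown to change what is reported. Literal use would tend towards over-reporting rather than missed reports, and sections 8.6 and 8.8.2 allow the grade to be revised later.

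**Conclusion.** The wording defect is certain from the text: timing alone satisfies Definitely, Probable is stricter, and a timing-only event can fit both Possible and Definitely. The consequence is conditional. If the definitions are applied literally, relatedness can be over-graded for individual adverse events and serious adverse events. The shift that matters is an event that would otherwise be Possible or lower rising to Definitely; confusing Probable with Definitely does not by itself change whether an event counts as related.

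The places affected are any summary of related events and, possibly, the causality input to expedited reporting. The most exposed moment is the initial report of a serious event: a grade is compulsory, section 8.8.2 accepts that information may be minimal, and timing may be all that is known.

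The number of events affected cannot be derived from the protocol, because it depends on how literally investigators read the line. Comparisons of all adverse events between arms, the primary endpoints and the sample size are unaffected. This is a point to correct because the rule is wrong as written and cheap to mend; it does not threaten the trial's main conclusions.

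**What to change.** Reconcile the two definitions in section 8.8.2 so that timing alone cannot meet Definitely and the grade is at least as strict as Probable. One wording that works is all the Probable conditions plus reappearance if product happens to have been reintroduced. This is a classification rule only and implies no planned re-exposure.

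State also that the highest grade whose full criteria are met applies. This sentence should be added together with the new definition: under the present text it would send every Probable event to Definitely.

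The change orders Definitely above Probable. It does not make every grade imply the one below, and need not, since Unlikely and Not Related are exclusive alternatives to the upper grades.

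The cost is a revised definition, the sentence on which grade applies, and matching eCRF help text. The downside is that Definitely would seldom be used, because the protocol describes no planned reintroduction of product.

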### 8.8.3 Assessment of Expectedness

- Expected** An adverse reaction, the nature or severity of which is consistent with the applicable product information (e.g. Investigators' Brochure for an unapproved medicinal product) or product insert.

**Unexpected** An adverse reaction, the nature or severity of which is not consistent with information in the relevant source document (e.g. Investigators' Brochure for an unapproved medicinal product) or product insert.

### **8.9 Follow-up of AEs and SAEs**

After the initial AE/SAE report, the Investigator is required to proactively follow up each Participant and provide further information to the Sponsor on the Participant's condition.

All AEs and SAEs documented at a previous visit/contact and are designated as ongoing, will be reviewed at subsequent visits/contacts. All AEs and SAEs will be followed until resolution, until the condition stabilises, until the event is otherwise explained, or until the Participant is lost to follow-up. Once resolved, the appropriate AE/SAE eCRF page(s) will be updated. The Investigator will ensure that follow-up includes any supplemental investigations as may be indicated to elucidate the nature and/or causality of the AE or SAE. This may include additional laboratory tests or investigations, histopathological examinations, or consultation with other health care professionals. New or updated information will be recorded on a new SAE form, with all changes signed and dated by the Investigator. The new or updated information should be resent to the Sponsor.

### **8.10 Post-study AEs and SAEs**

A post-study AE/SAE is defined as any event that occurs outside the AE/SAE detection period as defined in Section 8.4 "Time Period, Frequency, and Method of Detecting AEs and SAEs" of the protocol.

Investigators are not obligated to actively seek AEs or SAEs in former study Participants. However, if the Investigator learns of any SAE, including death, at any time after a Participant has been discharged from the study, and he/she considers the event reasonably related to the supplements, the Investigator will promptly notify the Sponsor.

## **9 Participant Completion and Discontinuation**

### **9.1 Participant Completion**

The definition of a completed Participant is if they have completed all visits according to the protocol or have met the rules in the following sections 9.2, 9.3 and 9.4.

### **9.2 Stopping Rules / Discontinuation Criteria**

Participants can be discontinued from study treatment and assessments at any time, at the discretion of the Investigator(s). Specific reasons for discontinuing a Participant from this study are:

- Withdrawal of informed consent
- Lost to follow-up
- Pregnancy in female Participant
- Protocol non-compliance

If the Investigator considers it is not in the best interest of the Participant to continue. Even if discontinued, Investigators will aim to follow up Participants at the pre-determined time points for trial assessments unless they specifically request in writing not to be conducted.

### **9.3 Voluntary Participant Withdrawal**

Participants are free to discontinue their participation in the study at any time, irrespective of reason. The Participant is not obliged to state his or her reason for withdrawal. However, all efforts will be made to see Participants in follow-up at pre-determined time points for trial assessments after stopping the intervention. If Participants are not willing to attend follow-up appointments then permission to maintain phone contact will be sought, unless they request in writing not to do so.

### **9.4 Early Termination of the Study**

The study may be terminated prematurely by the Principal Investigator (PI) or his/her designee and the Sponsor if:

- The number and/or severity of AEs justify discontinuation of the study
- New data become available which raise concern about the safety of the study drug, so that continuation might cause unacceptable risks to Participants.

In addition, the Sponsor and the administrator reserve the right to discontinue the trial prior to inclusion of the intended number of Participants, but intend only to exercise this right for valid scientific or administrative reasons.

After such a decision, the Investigator must contact all participating Participants within two weeks, and written notification must be sent to the HREC.

## **10 Case Report Form (CRF)**

Source notes will be kept in the Participant files at the Boden Institute. Data from the source notes and clinic visits will be entered into the eCRF according to the CTU standard operating procedures. An eCRF will be completed for each study Participant for those assessments which are written on paper. In the case of data and time stamped source data captured electronically, this will be used as the source. In order to retain confidentiality, Participants will be referred to in the eCRF by their Participant number and initials.

The completed eCRF's will be retained by the Investigator for a period of time as determined by local regulations. A copy of the eCRF will be given to the Sponsor at the end of the study.

